##### Hyperparameter Tuning

Each model class is characterised by a unique suite of hyperparameters that play a pivotal role in shaping performance. Manual trial-and-error to configure these values is computationally irreproducible and prone to bias [112]. To avoid obfuscating our models’ internal architectures, we will automate hyperparameter optimisation using grid search within the predefined hyperparameter search spaces tabulated below. The search spaces are intentionally small, as limiting the number of adjustable elements is another means to impose constraints on complexity (Table 2).

##### Model Building LR and XGBoost

We will instantiate LR with L2 regularisation and default hyperparameters (i.e., C = 1, max_iter = 100, solver = ‘lbfgs’), and XGBoost with default hyperparameters (i.e., n_estimators = 100, learning_rate = 0.1, max_depth = 3, objective = ‘binary:logistic’).

The AF dataset will be randomly split into two parts: training (***T***, 75%) and test sets (***t***, 25%), ensuring that the distribution of outcomes is preserved across both sets. LR and XGBoost models will each be trained, hyperparameter-tuned, and retrained on the training set (***T***), while the independent test set (***t***) will be withheld for final evaluation (Figure 1).

To achieve robust final models, we will employ nested cross-validation (CV) for training and hyperparameter tuning. Nested CV is particularly effective for small to moderately sized datasets because it promotes generalisability by ensuring that the hyperparameter tuning process does not contaminate the internal evaluation phase [113]. To this end, a 5 × 2 setup will be utilised, consisting of 5-fold CV in the outer loop and 2-fold CV in the inner loop (Figure 2). The set ***T*** will first be split into five equal parts. In each fold of the outer loop, one part (20% of ***T***) will serve as the intra-model test set ***T_t_*** while the remaining 80% will serve as the intra-model training set ***T_T_***. Each outer loop iteration will be subjected to an inner loop that further splits ***T_T_*** into two equal parts, using one as the true training set ***T_T_train_*** and the other as the validation set ***T_T_val_***, and alternating them over the two folds. The primary selection metric in the inner CV will be log loss (binary cross-entropy), with ties broken by calibration performance (Brier score).

Instantiating the models using the hyperparameters determined by the above procedure, we will retrain them in order to leverage all patients in ***T*.** The resulting models will be considered final and subjected to evaluation on ***t*** in the next section (see “Model Evaluation”). At this stage, training performance will be recorded. Specifically, we will report the area under the receiver operating characteristic curve (AUC), F1 score, accuracy, precision, sensitivity, and specificity. Coefficients and ORs (exponentiated coefficients) with 95% confidence intervals (CIs) will be reported for LR, and the hierarchy of predictor variables in descending order of gain (its internal feature importance metric) will be provided for XGBoost. Individual decision trees within the XGBoost model will supplementarily be made available.

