The sample sizes derived from steps 1, 2, 3, and 4 were 288, 344, 680, and 459 patients, respectively. We therefore deemed a minimum total sample size of 680 patients necessary for CPR development. Given that our sample size is 2763 patients and the fact that we will perform validation and updating (and not development from scratch), we contend that our regression analyses are adequately powered. Of note, 75% of our dataset (*n* = 2072 patients) will be used for regression model training and the remaining 25% (*n* = 691 patients) will be reserved for testing. The fact our test set alone exceeds the required 680 patients further supports our sample size.

ML and DL techniques are inherently more data-intensive than regression [85]. This is because the number of predictors they consider far exceeds that of regression, even when the same set of predictors is considered, because they examine multiple interaction terms [84]. Unfortunately, guidance for a priori sample size calculations is currently lacking for most ML/DL techniques [86]. However, if closely related data are readily available, it has been suggested that inspecting model learning curves in the related dataset can be valuable to estimate the required sample size for the main dataset [87,88]. We will therefore explore the observed power of our non-regression models by means of learning curves on our non-AF dataset, as well as via a key information theoretic metric: Kullback–Leibler (KL) divergence.

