Primary: How well does CHA_2_DS_2_-VASc capture 90-day AFAIS recurrence risk in terms of discrimination, calibration, and clinical utility? (Clinical utility performed against updated CPRs, see Tables 3 and 4.) Secondary: How well does CHA_2_DS_2_-VASc capture: 7-day recurrence, 7- and 90-day HT, 90-day decline in functional status, and 90-day all-cause mortality? Exploratory: How well does CHA_2_DS_2_-VASc capture 90-day recurrence and secondary outcomes for non-AF AIS patients?	Primary: Discrimination of CHA_2_DS_2_-VASc for 90-day AFAIS recurrence risk is unsatisfactory (AUC < 0.6), at worst, and modest (<0.7), at best. Calibration for 90-day recurrence also leaves much room for improvement. Secondary: As above.	Discrimination assessed using AUC and calibration curves. Calibration assessed using calibration curves, slopes, and Brier scores. Additional metrics: F1 score, accuracy, precision, sensitivity, specificity, Youden index, PPV, NPR, PLR, NLR.	Primary: A minimum of 680 patients deemed necessary, see Appendix S5.3 in Supplementary Materials file S3. Entire AF dataset will be used, comprising 2763 AFAIS patients. Secondary: As above. Exploratory: Entire non-AF dataset will be used, comprising 7809 AIS patients.	Compute AUCs with 95% CIs using 1000 bootstrap replicates. Produce calibration curves (and report calibration slopes) to illustrate calibration. Calibration curves also serve as alternative to ROC curves, as they illustrate true and false positive rates across different risk thresholds and thus help visualise discrimination. Compute Brier scores. Compute additional metrics.	Discrimination for each outcome will be classified as follows [101]: AUC of 0.81–0.90 = good, 0.71–0.80= fair, 0.61–0.70 = modest, and 0.51–0.60 = poor. In practice, calibration is more vulnerable to geographic and temporal heterogeneity than discrimination [102,103,104,105]. We thus stress that calibration is at least as important as discrimination [77,102]. Clinical utility via DCA will go beyond discrimination and calibration, considering them both at the same time [106], as well as individual preferences.

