##### Model Evaluation Test Set

The test set ***t***, disjointed from the set used in model building, will be used to evaluate and compare the performance of our final LR, XGBoost, and MLP models. As a randomly sampled subset of the development cohort, this test set will serve as an internal validation tool. Differences between test and training performance will also be reported, as this will be informative on the degree of overfitting to the training set [60].

The discriminative performance of each model will be reported using the AUC. AUCs will be reported with 95% CIs computed as the mean of 1000 bootstrap replicates ± 1.96 standard deviations. Since the AUCs will be derived from the same test set, we will also use DeLong’s method, a non-parametric approach to constructing CIs that accounts for implicit correlation between the underlying ROC curves [114].

Calibration will be investigated graphically using calibration curves. Calibration slopes and Brier scores will also be reported.

Additionally, F1 score, accuracy, precision, sensitivity, and specificity will be reported. Youden index, positive predictive value (PPV), negative predictive value (NPR), positive likelihood ratio (PLR), and negative likelihood ratio (NLR) will be supplementarily provided.

Coefficients and ORs will be tabulated for LR, and the hierarchy of predictor variables in descending order of gain will be provided for XGBoost. Individual decision trees within the XGBoost model will supplementarily be made available.

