##### CPR Evaluation

We will evaluate the CPRs on the test set ***t*** using discrimination, calibration, and clinical utility. The same methodology previously applied to CHA_2_DS_2_-VASc will be used to assess the discrimination and calibration of the newly developed CPRs. See Section 2.12.4. Clinical utility will be measured using net benefit (NB) via decision curve analysis (DCA). Although a CPR with better discrimination and calibration should, in theory, better guide clinical management, discrimination and calibration cannot determine whether a CPR aids decision making or which of several CPRs leads to better decisions. This is especially true when some CPRs have better discrimination and others better calibration. The shortcomings of conventional measures of performance are due to the fact that they do not incorporate information on consequences. DCA incorporates consequences by considering the tradeoffs between the benefits of true positives and the harms of false positives across a range of risk thresholds that reflect a spectrum of possible patient and clinician preferences [100]. It achieves this by calculating the NB for each risk threshold (*p**t*), which is defined as the number of true positives corrected for the number of false positives weighted by the odds of the risk threshold, all divided by the sample size (*N*) [124]. This is equivalent to the proportion of true positives in the absence of false positives (i.e., perfect specificity). To effectively use CPRs in clinical management, it is necessary to specify the risk thresholds at which intervention would be warranted. For early secondary prevention of AFAIS, oral anticoagulation is the treatment, and risk thresholds within 0.01—0.20 are reasonable. We will thus calculate the true positives and false positives for each CPR across the 0.01–0.20 risk threshold range and compute NB using the following formula:$$NB=\frac{\;\mathrm{True}\;\mathrm{positives}\;}{N}-\frac{\;\mathrm{False}\;\mathrm{positives}\;}{N}\left(\frac{p_{t}}{1-p_{t}}\right).\;$$

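### Outer-fold results are not among the performance listed for the training set, and the step that turns SHAP values into CPR points is never resampled

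*Protocol article*

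**What the plan says.** All places are in the protocol article.

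- **Model Building, LR and XGBoost.** The cross-validation is laid out as "a 5 × 2 setup will be utilised, consisting of 5-fold CV in the outer loop and 2-fold CV in the inner loop". In each outer iteration "one part (20% of *T*) will serve as the intra-model test set". The reason given for nesting is that "it promotes generalisability by ensuring that the hyperparameter tuning process does not contaminate the internal evaluation phase".
- **Same section, after tuning.** The models are refitted on all of T and "At this stage, training performance will be recorded". The metrics listed are AUC, F1, accuracy, precision, sensitivity and specificity. Outer-fold results are not listed.
- **MLP section and Table 4.** Two variants are trained, one with all layers fine-tuned and one with the pretrained layers frozen. Table 4 says that training performance informs which one is kept.
- **Model Evaluation, Test Set.** Of the 25% hold-out set t, the article says "this test set will serve as an internal validation tool". Overfitting is described by the difference between test and training performance.
- **CPR Development.** Points come from where eight mean SHAP values fall relative to their own percentiles. Interaction points come from the 90th percentile of 28 mean interaction values, with room for domain knowledge. Tier boundaries may be adapted after the dot plot has been inspected.
- **CPR Evaluation.** "We will evaluate the CPRs on the test set" t. On the same set the CPRs are ranked by net benefit and the best three are identified.

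**The concern.** Nested cross-validation exists to give an estimate of performance that tuning has not biased. Here the fits are made, but the article assigns no reporting role to the scores they produce. What it lists for T is the in-sample fit of the refitted model, which is optimistic. For LR and XGBoost this only describes overfitting. For the MLP it informs a decision, and in-sample metrics tend to favour the more flexible variant.

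The second gap concerns the CPRs, which are the product of the study. Three models give two CPRs each, so six are compared on the 691 patients, together with CHA2DS2-VASc. Reporting the winner on the set that picked it carries selection optimism. Percentile cut-offs on eight values, and on 28 values, can also move features between tiers when the data change slightly. Nothing in the plan would show how often that happens.

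**Working it through.** **Inputs.** AF cohort 2763, split 75/25, five outer folds (2.7; Model Building). Recurrence between 5% and 25% (2.7). The AUC of 0.65 is an assumption; it lies in the plan's modest class (0.61–0.70).

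**1. The plan's own figures.** 2763 × 0.75 = 2072.25 and 2763 × 0.25 = 690.75, so 2072 and 691 are confirmed. The 680 that section 2.7 compares with the test set is also reproduced, if one assumes 8 predictors, shrinkage S = 0.9 and R² = 0.10: 8 / [(0.9 − 1) × ln(1 − 0.10/0.9)] = 679.2, rounded up to 680. That is a requirement for fitting a model with little shrinkage. It says nothing about how precisely 691 patients measure performance.

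**2. Precision of an AUC of 0.65** (Hanley–McNeil). With n1 events and n0 non-events,

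SE² = [A(1 − A) + (n1 − 1)(Q1 − A²) + (n0 − 1)(Q2 − A²)] / (n1 × n0), where Q1 = A/(2 − A) and Q2 = 2A²/(1 + A).

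For A = 0.65: A(1 − A) = 0.2275, Q1 − A² = 0.0590, Q2 − A² = 0.0896.

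Worked case, n = 691 at 5%: n1 = 34.55 and n0 = 656.45. The numerator is 60.95 and n1 × n0 = 22,680. SE = 0.0518, and the half-width is 1.96 × 0.0518 = 0.102.

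| Recurrence | Events in 691 | Half-width | Events in 2072 | Half-width |
|---|---|---|---|---|
| 5% | 35 | 0.102 | 104 | 0.059 |
| 10% | 69 | 0.073 | 207 | 0.042 |
| 25% | 173 | 0.049 | 518 | 0.028 |

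The standard error falls by 1 − √(691/2072) = 42%. At 5% recurrence, the interval on t runs from about 0.55 to 0.75 and so reaches into the plan's poor, modest and fair classes.

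The figures for 2072 are approximate. The out-of-fold scores come from five fits, each on 80% of T (about 1658 patients), whereas the formula treats them as one model.

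**3. Bias.** A simulation of 400 runs used ridge LR with fixed penalty (C = 1), eight independent binary predictors, assumed effects and a true AUC of about 0.59–0.60. The outer-fold AUC was the mean over five folds.

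| AUC measured on | Bias at 5% | RMSE at 5% | Bias at 25% | RMSE at 25% |
|---|---|---|---|---|
| T, in-sample | +0.042 | 0.049 | +0.009 | 0.016 |
| T, outer folds | −0.005 | 0.035 | −0.005 | 0.017 |
| t (691) | −0.002 | 0.052 | −0.001 | 0.025 |

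The outer-fold result is slightly pessimistic and has a smaller error than the single test set. For plain LR the in-sample optimism matters at 5% and is small at 25%. XGBoost and the MLP were not simulated.

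**4. What the outer folds cover.** SHAP, tiers and interaction points are applied once, to the final models. The planned outer folds therefore hold out-of-fold predictions of LR, XGBoost and the MLP, and none of any CPR. The gain in step 2 extends to the CPRs only if their construction is repeated in each fold.

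**The case against.** A locked hold-out set after cross-validated tuning is a common and defensible design. Several points on that side stand.

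- **Silence.** A reader might infer that the plan discards three quarters of its honest evidence (2072/2763 = 75%). The article does not say that outer-fold results will be withheld. Its within-fold imputation rule makes most sense if those folds are scored, and the two workflow figures are not shown. Still, the list of what is reported at this stage is specific and omits them, and the role of internal validation is given to t.
- **Models, not CPRs.** The same inference fails for the CPRs, because no out-of-fold CPR results would exist as planned.
- **Other evaluations.** A reader might also infer that the CPRs are judged only once, on 691 patients. That holds for the primary outcome in AF patients. The LR and XGBoost CPRs are also evaluated on the 7809 non-AF patients. For secondary outcomes Table 3 uses all 2763 AF patients, although that includes T. A separate external validation study is promised.
- **Visible uncertainty.** Bootstrap and DeLong intervals on t will show the imprecision, and the gap between test and training is a legitimate overfitting measure for LR and XGBoost.
- **Procedure versus product.** Each fold may give different points, so pooled CPR results describe the procedure and not the one CPR to be published.

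These points narrow the concern. They do not remove the use of training metrics to choose the MLP variant, the ranking and reporting on one split, or the missing check on the stability of the points.

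**Conclusion.** The concern holds in a limited form, as an improvement the plan should make. For T the article lists in-sample performance only, although nested cross-validation yields nearly unbiased model results there at no further cost. Training metrics inform one modelling choice. For the primary outcome in AF patients, the CPRs are ranked and reported on the same 691 patients, and the construction of the points is never resampled.

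For model AUCs, the half-width is about 0.10 (5% recurrence) to 0.05 (25%) on t, against about 0.06 to 0.03 from the outer folds. This rests on an AUC of 0.65, the plan's recurrence range and the Hanley–McNeil approximation. The size of the selection optimism, and the instability of the points, cannot be computed from the article.

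**What to change.** 1. **Models.** Report outer-fold AUC, calibration slope and Brier score for LR, XGBoost and the MLP. Choose between the fine-tuned and frozen MLP on outer-fold or validation results. Keep training performance only as the reference for overfitting.
2. **CPRs.** Turn the choice of tier boundaries and interaction pairs into fixed rules. Compute the SHAP values behind the points on training data only: the Global Interpretation section summarises them across the test set, and the CPR Development section names no other set, so t may otherwise help to shape the CPRs. Then repeat the whole construction inside each outer fold of T. Report out-of-fold discrimination, calibration and net benefit, and how often each feature receives each point value.
3. **Selection.** Choose the leading CPR from these results and confirm it once on t.

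Item 1 needs wording only, because the fits are already planned. Item 2 costs five further SHAP-to-points runs per model, and gives up the freedom to tailor tiers after seeing the plot. The 75/25 split is unchanged, so the final estimate on t keeps its present width. What improves is that the estimate no longer carries selection optimism and that the stability of the points is known.

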##### MLP

MLP will be instantiated with default hyperparameters (i.e., optimizer = Adam(learning_rate = 0.01), loss = ‘binary_crossentropy’, metrics = [‘AUC’]), units = 32, hidden_layers = 2, activation = ‘relu’, kernel_regularizer = l2(0.01), dropout = 0.2 for the pretrained model; and the best hyperparameters found during pretraining for the fine-tuned model, with the exception of learning_rate = 0.00001).

Unlike the AF dataset, the non-AF dataset will not undergo random splitting. Rather, the MLP will be trained, hyperparameter-tuned, and retrained on the whole non-AF dataset to yield the so-called pretrained model. As above, 5 × 2 nested CV will be implemented and the best hyperparameters will be used to retrain the model on all non-AF patients.

The pretrained model will then be evaluated (AUC, F1 score, precision, sensitivity, specificity) and its last layer(s) will be removed, which are expected to be the more task-specific ones (i.e., non-AF patient-centric). These layers will be replaced by new, naive layers that culminate in an output layer with two neurons, given that we are performing probabilistic binary classification. The resulting neural network will be trained on ***T***, the training set of the AF dataset. Two strategies will be tried: fine-tuning of all layers, including pretrained ones (albeit with very low learning rates), and freezing of pretrained layers, with training confined to the newly added layers. In either case, the training phase will again employ 5 × 2 CV and the fine-tuned model will be retrained on ***T*** as a last step. Early stopping will be implemented with a patience parameter of 10 epochs, monitored on the validation loss during training.

Training performance will be reported using AUC, F1 score, accuracy, precision, sensitivity, and specificity. AUC, F1 score, accuracy, precision, and sensitivity will be used to inform whether the purely fine-tuned or the frozen model will be retained for evaluation on ***t***.

For reproducibility, matched random seeds will be set and reported across LR, XGBoost, and MLP models.

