
**Table 4 jcm-14-07327-t004:** Updating analyses; secondary.

Questions	Hypotheses	Outcome Measures	Sampling Plan (*N*, Power Analyses)	Analysis Plan	Interpretation Given to Different Outcomes
Primary: Does the acute context of AFAIS, and the importance of the index event, call for a CPR bespoke to early secondary prevention? In other words, are the main effects of the constituent features of CHA_2_DS_2_-VASc different post-stroke? Besides main effects, are there synergistic or other non-linear interaction effects between stroke history and the constituent features of CHA_2_DS_2_-VASc that can further improve prediction of 90-day AFAIS recurrence? Secondary: How do CPRs trained to capture 90-day AFAIS recurrence perform with regard to secondary outcomes (7-day recurrence, 7- and 90-day HT, 90-day decline in functional status, and 90-day all-cause mortality)?	Primary: MLP can capture the main effects of the constituent features of CHA_2_DS_2_-VASc in the context of secondary prevention, as well as complex functional relationships between stroke history and the other features. Its output can be employed to construct CPRs that outperform CHA_2_DS_2_-VASc for predicting 90-day recurrence in AFAIS patients. Specifically, fair (AUC <0.8) to good (<0.9) discrimination can be achieved for this high-risk group, alongside improved calibration and clinical utility relative to CHA_2_DS_2_-VASc. Secondary: The resulting CPRs also outperform CHA_2_DS_2_-VASc for predicting secondary outcomes.	See Table 3.	Learning curve analysis and KL divergence will afford post hoc insight on suitability of sample size. Data augmentation via transfer learning is particularly valuable for DL models like MLP, which are very data-hungry. Entire non-AF dataset will be used in pretraining phase, comprising 7809 AIS patients. 75% of AF dataset (***T***) will be used in fine-tuning phase, comprising 2072 AFAIS patients. Remaining 25% of AF dataset (***t***, 691 patients) will be withheld as test set.	The MLP model will leverage information within the non-AF patient dataset during pretraining. Non-AF AIS patients, who were not included in training the LR and XGBoost models—and therefore in no capacity informed the CPRs constructed thus far—may improve CPR generalisability and clinical utility. We contend our use case is well-suited to transfer learning given that the features of CHA_2_DS_2_-VASc are known to increase risk of AIS in patients without AF, and it has been reported to be equally predictive in the absence of AF [40]. MLP will be instantiated using default hyperparameters and undergo training, hyperparameter tuning, and retraining on the entire non-AF dataset to yield the pretrained model. The pretrained model will be evaluated (AUC, F1 score, precision, sensitivity, specificity) and its last layer(s) removed. These will be replaced by new, naive layers that culminate in an output layer with two neurons. The resulting neural network will be trained on the training set ***T***. Two strategies will be tried: fine-tuning and freezing. In either case, the training phase will again employ nested CV (5 × 2) and the fine-tuned model will be retrained on the AF training set. Training performance will be reported using AUC, F1 score, accuracy, precision, sensitivity, and specificity, used to inform whether the purely fine-tuned or the frozen model will be retained for evaluation on the test set ***t***. To derive CPRs from the MLP model’s output, SHAP will quantify main and interaction effects of predictor variables. Main effects, represented by mean SHAP values, will be used to rank and assign scores to each predictor. Interaction effects, captured through SHAP interaction values, will further refine our CPR by identifying significant synergistic or redundant relationships between predictors. These interactions will be incorporated into an ‘augmented CPR’ in the form of accompanying rules. Both non-augmented and augmented CPRs will be evaluated on the test set ***t*** in terms of discrimination, calibration, and clinical utility. The CPRs will be compared on the basis of clinical utility to one another, LR- and XGBoost-informed CPRs, CHA_2_DS_2_-VASc, and default strategies (‘treat all’ and ‘treat none’). Test tradeoff analysis will be performed. Secondary: CPRs (and not the MLP model) will be evaluated on the test set ***t*** for each secondary outcome via discrimination, calibration, and clinical utility.	See Table 3.

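### The fully fine-tuned or frozen MLP is chosen on training performance, an in-sample criterion that tends to favour the more flexible network and conflicts with Table 2 and the held-out log-loss rule.

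*Protocol article*

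**What the plan says.** The MLP section of the Protocol article describes two strategies for the network pretrained on non-AF patients: tune every layer at very low learning rates, or freeze the pretrained layers and train only the new ones. Both go through 5 × 2 cross-validation, and the network is then retrained on the whole AF training set **T**. After this the text reads "Training performance will be reported using AUC, F1 score, accuracy, precision, sensitivity, and specificity". The next sentence takes the same list without specificity and makes it the basis for deciding which network goes on to the test set **t**; it ends on these terms: "precision, and sensitivity will be used to inform whether the purely fine-tuned or the frozen model will be retained".

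The analysis plan in Table 4 joins the two steps in one sentence, which begins "Training performance will be reported using AUC, F1 score, accuracy, precision, sensitivity, and specificity, used to inform whether the purely fine-tuned or the frozen". It counts specificity among the deciding metrics; the MLP section does not.

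Three other places bear on the choice:

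- Model Building LR and XGBoost: "The primary selection metric in the inner CV will be log loss (binary cross-entropy), with ties broken by calibration performance", measured by the Brier score.
- Table 2: freezing of layers is a row of the MLP fine-tuning search space, next to units, learning rate and dropout, with a custom implementation in place of values. The Hyperparameter Tuning section says that these spaces are searched by grid.
- Model Evaluation Test Set: "Differences between test and training performance will also be reported, as this will be informative on the degree of overfitting to the training set".

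**The concern.** For a given architecture, the frozen network is the fully tuned one with part of its weights held fixed. If the two are compared on the data used to fit them, the one with more freedom has an advantage that says nothing about new patients. The protocol itself reads the gap between training and test performance as a sign of overfitting, so it accepts that training figures are optimistic. Here it lets those figures make a modelling decision.

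Only the retained network is evaluated on **t**, passed to SHAP and turned into the two MLP-based CPRs, which are then ranked by net benefit against the others. If the choice is tilted, a network that generalises less well may be the one carried forward.

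The criteria raise a further problem. The plan treats calibration as at least as important as discrimination, yet none of the five or six deciding metrics measures it. No rule says what happens when they disagree.

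**Working it through.** **1. Is the criterion in-sample?** The order in the MLP section is cross-validation, retraining on **T**, training performance, choice. For LR and XGBoost the protocol places the same term after retraining on all of **T**: "At this stage, training performance will be recorded". Table 4 names training performance as the basis of the choice. With the overfitting remark in Model Evaluation Test Set, the natural reading is apparent performance on **T**.

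**2. Size of T.** 0.75 × 2763 = 2072.25 and 0.25 × 2763 = 690.75, which reproduces the protocol's 2072 and 691. With recurrence of 0.05 to 0.25 (Handling Class Imbalance), **T** holds 2072 × 0.05 = 103.6, about 104 events, to 2072 × 0.25 = 518 events.

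**3. Difference in freedom.** Take the default network: two hidden layers of 32 units and two output neurons. Assume 9 inputs, because Variable Encoding creates three age indicators and drops one only in logistic regression.

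- All layers trainable: (9×32+32) + (32×32+32) + (32×2+2) = 320 + 1,056 + 66 = 1,442 weights.
- Frozen, only the output layer new: 66 weights.
- Frozen, second hidden layer also new: 1,056 + 66 = 1,122 weights.

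The protocol removes an unspecified number of last layers, so the frozen strategy trains between 66/1,442 = 5% and 1,122/1,442 = 78% of the weights. With the eight predictors counted under CPR Development, the full total is 1,410 and the range is much the same. The direction is fixed; the size of the contrast is not.

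**4. Direction of the selection error.** An illustrative simulation used 300 runs per event rate, n = 2072, eight binary features and a main-effects truth. It compared a rigid logistic model (eight terms) with a flexible one (the same terms plus pairwise products). These stand in for the two strategies; they are not the MLP.

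| Event rate | Training AUC, flexible / rigid | New-data AUC, flexible / rigid | Flexible chosen on training AUC | Flexible chosen on 5-fold CV AUC |
|---|---|---|---|---|
| 0.05 | 0.677 / 0.612 | 0.538 / 0.558 | 100% | 28% |
| 0.10 | 0.642 / 0.601 | 0.556 / 0.576 | 100% | 15% |
| 0.25 | 0.614 / 0.590 | 0.558 / 0.573 | 100% | 9% |

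The flexible model was better on new data in at most 0.3% of runs. On average, training AUC put the two models in the wrong order at every rate.

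**5. Consistency within the protocol.** Table 2 with the inner cross-validation rule would settle freezing by held-out log loss, then Brier score. The MLP section and Table 4 settle it by training AUC and classification metrics. Both cannot govern the same choice.

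**The case against.** The strongest reply is that the remedy is already in the plan: Table 2 lists freezing in the search space, so it would be tuned like any other hyperparameter. That holds as far as it goes, but the MLP section and Table 4 then state a different rule for the same decision. Table 2 shows a contradiction; it does not cure it.

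Second, the selection sentence in the MLP section does not itself contain the word training, and the explicit timing is given for LR and XGBoost. A reader could take the metrics to be outer-fold results. Table 4 speaks against this, and if it was the intention, the wording still needs correcting.

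Third, one might infer that training fit must favour full fine-tuning however the network generalises. The document does not support that. Nesting guarantees a better fit only at the optimum of the training loss, and here there is early stopping on validation loss with a patience of 10 epochs, L2, dropout and fine-tuning learning rates from 0.000001 to 0.0001. In a small network check (25 runs per learning rate, a 9-32-32 network, about 9% events, at most 150 epochs), full fine-tuning had the higher training AUC in 20% of runs at 0.00001, with neither strategy converged by the cap, and in 92% at 0.0001. Those proportions depend on the assumed settings, but they show a tendency and not a certainty.

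Fourth, it would be wrong to call the criteria purely threshold-dependent, because AUC heads both lists.

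**Conclusion.** The point stands as a flaw in a secondary analysis. As written, the choice between the two strategies is made in-sample, tends to favour the one with more trainable weights, ignores calibration, and contradicts both Table 2 and the protocol's own held-out selection rule.

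Its size for this MLP cannot be derived from the document. The simulation shows only the direction, under a main-effects truth and with logistic stand-ins. The weight counts depend on how many layers are replaced and should be read as a range.

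Three stronger conclusions are not supported. The estimate on **t** is not biased by this rule, because **t** plays no part in the choice. Transfer learning is not defeated, because both candidates start from the pretrained weights. The primary LR and XGBoost analyses are untouched. What remains is the risk that the less generalisable of two networks is the one turned into the MLP-based CPRs.

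**What to change.** State once that frozen versus fully fine-tuned is a hyperparameter of the fine-tuning stage, as Table 2 implies. Choose it by cross-validated (held-out) log loss within **T**, with the Brier score for ties, and then retrain the chosen strategy on all of **T**.

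In the MLP section and in Table 4, delete the statements that the training metrics inform the choice. Keep those metrics for description, with one list in both places. In Table 2, replace the custom-implementation entry with the options compared, and say how many layers are removed and added.

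The cost is wording. The 5 × 2 cross-validation is already planned for both strategies and the selection metric is already defined for the other models. The change should be made before results are seen.
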